## Abstract

**Background:**

Depression is one of the most debilitating and costly mental disorders. There is increasing evidence for the efficacy of online self-help in alleviating depression. Knowledge regarding the options of combining online self-help with inpatient psychotherapy is still limited. Therefore, we plan to evaluate an evidence-based self-help program (deprexis®; Gaia AG, Hamburg, Germany) to improve the efficacy of inpatient psychotherapy and to maintain treatment effects in the aftercare period.

**Methods/design:**

Depressed patients (n = 240) with private internet access aged between 18 and 65 are recruited during psychosomatic inpatient treatment. Participants are randomized to an intervention or control group at the beginning of inpatient treatment. The intervention group (n = 120) is offered an online self-help program with 12 weekly tasks, beginning during the inpatient treatment. The control group (n = 120) obtains access to an online platform with weekly updated information on depression for the same duration. Assessments are conducted at the beginning (T0) and the end of inpatient treatment (T1), at the end of intervention (T2) and 6 months after randomization (T3). The primary outcome is the depression score measured by the Beck Depression Inventory-II at T2. Secondary outcome measures include anxiety, self-esteem, quality of life, dysfunctional cognitions and work ability.

**Discussion:**

We expect the intervention group to benefit from additional online self-help during inpatient psychotherapy and to maintain the benefits during follow-up. This could be an important approach to develop future concepts of inpatient psychotherapy.

**Trial registration:**

ClinicalTrials.gov Identifier: NCT02196896 (registered on 16 July 2014).

## Background

Depression poses one of the most serious health problems on a worldwide basis [1]. While effective evidence-based treatments have been established, only a minority of patients receive them. Thus, there have been many efforts to deliver online interventions, which have the potential to be widely available. Nevertheless, it is still unclear if and how people use the internet if they have mental health problems. In a recent survey in the German population, Eichenberg and colleagues [2] found that more than one quarter (26.3% of the general population resp. 43.7% of the internet users) consider seeking help online, but only a few (2.2%) already used psychological counseling or could imagine (<10%) seeking support online in case of psychiatric strain. Indeed, positive effects of internet-based interventions on symptoms have been established regarding depression. In two recent meta analyses effect sizes have been reported, with small effects for the difference between self-guided psychological treatment of depression and control groups (d = 0.28, seven randomized controlled trials [3]) and moderate effects (d = 0.56; 19 studies [4]) for the post-treatment effects. For anxiety disorders another meta-analysis found an overall effect size of computer-aided psychotherapy compared with non-computer-aided psychotherapy of d = 1.08 (23 randomized controlled trials [5]). A considerable number of studies and meta-analyses have found that guided self-help for depression is effective compared to untreated control conditions [3] and that it may be as effective as face-to-face treatments [5,6].

Most research has focused on guided online self-help interventions, including support by a professional therapist or coach. However, as determined by a meta-analysis [4], supported interventions increased retention compared to studies without support, and this leads to the recommendation of blended approaches in the internet-based treatment of depression. Johansson and Andersson [7] also found a strong correlation between the degree of therapist support and outcome of internet-based psychological treatments of depression. Evidence regarding the effectiveness of online-based treatments as a complement to regular medical or psychotherapeutic care, however, is limited and contradictory [7].

deprexis® is a new and interactive internet-based self-help program that does not require therapist support. It has found strong support in the treatment of depressive disorders [7-9]. However, its efficacy has not yet been investigated as an adjunct to inpatient psychotherapy. We have only found one published study protocol in which it is planned to use deprexis® as an adjunct to psychological treatment in various settings [10].

Depression is the most frequent diagnosis in inpatient psychotherapy [11], which is indicated when depression is severe, significantly impairing activities of daily living and work ability or if it is compounded by other mental disorders [12]. Depression can be improved considerably by inpatient psychotherapy [13,14]. However, despite intensive treatment, many patients do not fully remit in a time frame of 4 to 8 weeks. Partially remitted or subclinical depression is known to be a risk for relapse [15], particularly when no immediate follow-up outpatient treatment is provided. Indeed, following discharge, a substantial proportion of patients need to search for a psychotherapist, and have to wait for adequate treatment for several months. An internet-based treatment could bridge this gap and offer immediate support after inpatient treatment. A large randomized controlled trial (n = 400 patients) could show that treatment effects were maintained until a 12-month follow-up after inpatient psychosomatic treatment with a 12-week transdiagnostic internet-based maintenance treatment compared to treatment as usual [16]. Internet-based interventions are further effective in preventing relapse; for example, with internet chat groups following inpatient psychotherapy [17] or a 10-week internet-based cognitive behavior therapy compared to a control group [18].

We assume that adding an online self-help program to standard inpatient treatment could increase the efficacy of inpatient treatment and also bridge the gap to outpatient treatment. Therefore, this trial aims to determine the feasibility and effectiveness of supplementing online self-help for depressed patients during and immediately after inpatient psychotherapy.

## Methods

### Participants

At admission to inpatient psychotherapy, patients are informed about the study. Those eligible are inpatients aged 18 to 65 years who have private internet access, sufficient German language proficiency, a score in the clinical range (>13) of the Beck Depression Inventory-II (BDI-II) [19] and a clinical diagnosis of depression (International Statistical Classification of Diseases and Related Health Problems, 10th revision (ICD-10), codes F32.x, F33.x, F34.1, F43.2), as assessed by the individual therapist of the patient. Those excluded are patients suffering from psychosis, current alcohol or drug addictions, borderline, antisocial, schizoid and schizotypal personality disorders, anorexia nervosa, lifetime diagnoses of schizophrenia, schizoaffective, bipolar or organic mental disorder.

The study assistant screens every patient at intake who fulfils the BDI-II criteria in the standard intake assessment and who is diagnosed with a depressive disorder by his or her therapist regarding inclusion and exclusion criteria.

Data for patients who are eligible for participation and have given written informed consent are coded, and patients are randomized by the study center. Study information is given to the patients by a study assistant. They are provided with their access codes for the online self-help program or the online platform of the control condition and receive a short introduction to their respective treatment condition.

The Study Center of Mental Disorders at the University Medical Center of the Johannes Gutenberg-University Mainz is responsible for storing personal data and randomizing participants. Administration of the internet-platform and allocation of the weekly information text in the control condition are managed by psychologists of the Department of Psychosomatic Medicine and Psychotherapy of the University Medical Center Mainz.

The clinical protocol and written informed consent were approved by the Ethics Committee of the Federal State of Rhineland Palatinate (Germany), which is responsible for the coordinating center in Mainz (Ref. No. 837.093.14(9332-F)). All procedures described in the clinical trial protocol (ClinicalTrials.gov identifier: NCT02196896) follow the International Conference on Harmonisation Good Clinical Practice guidelines and the ethical principles described in the current revision of the Declaration of Helsinki. The trial will be carried out in keeping with local legal and regulatory requirements.

The study platform containing the information for the control group and redirecting all participants to the website used for the online survey is located on a firewall-protected webserver which uses an SSL-encrypted (secure sockets layer) access to the MySQL-database containing the login information. SSL-encryption is a security standard widely used on the internet (for example, for online banking). All questionnaires will be administered via the online survey program SoSci Survey (https://www.soscisurvey.de) that uses SSL-coded internet connections as well. Furthermore, all patients use pseudonyms to login to the study platform. As no personal data are stored on the webserver, identification of the real identity of the user is not possible.

### Intervention

In addition to inpatient treatment (treatment as usual) consisting of individual and group psychotherapy, integrating body-oriented and creative psychotherapy interventions, as well as various adjunct treatments (for example, relaxation, patient education, exercising, therapeutic community) [20], participants in the intervention group receive access to a 12-week internet-based self-help treatment (deprexis®) that is described in detail elsewhere [21]. The self-help program consists of 10 modules, plus one introductory and one summary module. The modules combine cognitive and behavioral techniques with positive psychology, dream work and emotion-focused interventions. The contents of the modules are provided as a simulated dialogue, explaining and illustrating concepts and techniques, engaging the user in exercises, and continuously asking for user feedback. Provision of subsequent content is tailored to the users’ responses. Participants can work through the program at their own pace, as modules are not gradually made available at a specific schedule [10]. If desired by the user, the program automatically delivers helpful comments or reminders on a daily basis by SMS or email.

In the weekly treatment plan delivered to the patients by the clinic, two time slots are scheduled for the intervention per week on different weekdays. Participants work in a room with computer terminals at their own pace during these time slots. After discharge from the hospital, patients are eligible to continue the online self-help program free of charge for the remaining period (the program is accessible for a total of 12 weeks from first login).

### Control condition

All participants receive inpatient treatment (treatment as usual) as described above. Participants in the control condition additionally receive access to an online platform with freely available and reliable information regarding the diagnosis, etiology, course and treatment of depression, including self-help options. Information has been compiled with appropriate permissions from public domain sources, for example the patient version of the German medical guidelines or information provided by the German network on depression, health insurance companies or federal health agencies. In order to increase motivation and ease of studying, information is broken down into packages with specific topics, which are made accessible on a weekly basis. In order to ensure comparability to deprexis®, two time slots with the same duration are allotted for program participation during inpatient treatment. Participants may use the webpage over a period of 12 weeks.

### Assessment

Assessments are conducted at the beginning (T0) and the end (T1) of inpatient treatment, at the end (T2) of intervention and 6 months after randomization (T3; Figure 1). Screening is based on the BDI-II [19], a reliable and valid 21-item self-report scale of depression, during the past 2 weeks, together with ICD-10 diagnoses made by the individual therapist. At T0 patient characteristics (for example, education, employment, family status) will be taken from the basic documentation of the clinic. In addition to the BDI-II, the reliable and valid Patient Health Questionnaire (PHQ-9) is used to assess depression [22] along with the Generalized Anxiety Screener (GAD-7) [23]. Other self-report questionnaires assess self-esteem (Rosenberg Self-Esteem Scale, RSE) [24], quality of life (European Health Interview Survey Quality of Life 8 Item Index, EUROHIS-QOL 8) [25] and dysfunctional depression-related cognitions (Dysfunctional Attitude Scale, DAS) [26]. We further assess childhood trauma with the Childhood Trauma Questionnaire (CTQ) [27]. The Work Ability Index (WAI) [28] questions current work ability in relation to physical and mental job demands, and prognosis for the forthcoming 2 years. Structural psychological deficits are assessed by the short form of the OPD Structure Questionnaire (OPD-SQ) [29], and the therapeutic alliance by the Helping Alliance Questionnaire (HAQ) [30], with a patient as well as a therapist rating.

**Figure 1 Fig1:**
[figure not shown]
**Study design and time points of assessment.** TAU, treatment as usual.

At discharge (T1) and follow-up (T3) subjects fill out the BDI-II, PHQ-9, GAD-7, RSE, EUROHIS-QOL 8, WAI and the DAS. At discharge, we furthermore assess the HAQ, satisfaction with inpatient treatment, and acceptance of and satisfaction with deprexis® (intervention) or the online information (control condition). At the end of the intervention (T2) subjects fill out the BDI-II and a questionnaire concerning acceptance and satisfaction analogous to T1, including items assessing willingness to pay for the intervention (deprexis®). In addition, utilization of other treatments after the end of inpatient treatment will be measured at T3 (Table 1).

**Table 1 Tab1:** **Schematic overview of frequency and scope of the study visits**

	**Screening**	**Pretreatment**	**Discharge**	**End of Intervention**	**Follow-up**
Study visits		T0	T1	T2	T3
Written informed consent	X				
Screening questions	X				
BDI-II	X		X	X	X
GAD-7		X	X		X
PHQ-9		X	X		X
RSE		X	X		X
EUROHIS-QOL 8		X	X		X
DAS		X	X		X
CTQ		X			
WAI		X	X		X
OPD-SQ		X			
HAQ			X		
Satisfaction with intervention			X	X	
Utilization of other treatment					X
BADO		X	X		
Willingness to pay				X	
Adverse events		continuously	X	X	

BADO, basic documentation; BDI-II, Beck Depression Inventory-II; CTQ, Childhood Trauma Questionnaire; DAS, Dysfunctional Attitude Scale; EUROHIS-QOL 8, European Health Interview Survey Quality of Life 8 Item Index; GAD, Generalized Anxiety Screener; HAQ, Helping Alliance Questionnaire; OPD-SQ, OPD Structure Questionnaire; PHQ, Patient Health Questionnaire; RSE, Rosenberg Self-Esteem Scale; WAI, Work Ability Index.

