### Objectives and hypotheses

The purpose of this study is to determine the efficacy of an online self-help program (deprexis®) for enhancing standard inpatient psychotherapeutic treatment at the end of the intervention. We hypothesize that the online self-help group has a lower BDI-II score at the end of the intervention (primary outcome). We further assume that this effect will already be measurable at termination of inpatient treatment and will be maintained up to the 3-month follow-up (secondary outcomes).

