### Statistical methods

For the primary outcome criteria, analysis of covariance will be used to compare BDI-II scores at the end of treatment between the intervention and control condition, with baseline scores of the BDI-II as covariates.

Intent-to-treat analyses with multiple imputations to replace missing data as well as completer analyses will be conducted.

For the secondary analyses, self-report questionnaires (BDI-II, PHQ-9, GAD-7, RSE, EUROHIS-QOL 8, DAS, WAI, HAQ) will also be analyzed by analysis of covariance All analyses will be conducted on a two-sided level of significance of 0.05. Descriptive statistics showing the measurements over time will be presented whenever appropriate. In order to define the percentage of remitted patients, the reliable change index [36] will be computed. Patients with a post-treatment depression score in BDI-II below the cut-off of 13 and a reliable change regarding the reliable change index will be considered as remitted. Additionally, serious adverse events and drop-outs will be analyzed descriptively.

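### Table 1 schedules no adverse-event query at T3, although the secondary claim of a maintained effect runs to T3

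*Protocol article*

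**What the plan says.** All references are to the protocol article.

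- **Table 1** has its own row for adverse events: "Adverse events continuously X X". Read against the column heads, the word stands under T0, the marks under T1 and T2, and the T3 cell is empty.
- **Assessment** places the last two visits "at the end (T2) of intervention and 6 months after randomization (T3; Figure 1".
- **Assessment, text after Figure 1**, shows how much is collected at the last visit: "At discharge (T1) and follow-up (T3) subjects fill out the BDI-II, PHQ-9, GAD-7, RSE, EUROHIS-QOL 8, WAI and the DAS". It adds that "utilization of other treatments after the end of inpatient treatment will be measured at T3".
- **Objectives and hypotheses** expects that the effect "will be maintained up to the 3-month follow-up (secondary outcomes"). Outcomes lists BDI-II reduction at that follow-up among the key secondary endpoints.
- **Statistical methods** says that "serious adverse events and drop-outs will be analyzed descriptively". It gives no time window for this summary.
- **Outcomes** lists use of other treatment after the inpatient stay among the predictors of outcome.

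**The concern.** Benefit is measured and claimed to T3, while the last scheduled question about adverse events is at T2. A report could then say that the effect was maintained at 6 months and that serious adverse events did not differ between arms. The reader would not see that the first half of that sentence rests on about 26 weeks and the second on about 12. The gap also begins when access to either platform ends, and maintaining gains in aftercare is a stated aim in the Abstract.

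This cannot be repaired at the analysis stage. A statistical analysis plan can choose how to tabulate events, but it cannot recover events that nobody asked about. The point concerns the collection window that Table 1 sets out, not a detail that an article leaves to the full protocol.

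**Working it through.** The plan states no figure for the adverse-event window, so there is none to reproduce. The check is the length of the window and what else is recorded in it.

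**Inputs**

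- T3: 6 months after randomization (Assessment), taken as 26 weeks; 24 weeks if a month is counted as 4 weeks.
- T2: end of the 12-week program, which runs from first login (Intervention). Taken as week 12 after randomization. First login may come later, so up to week 14 is allowed as an assumption.
- Inpatient stay: 4 to 8 weeks. This comes from a general sentence in Background and is not a fixed trial parameter.

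**Share of follow-up without a scheduled query** = (T3 − T2) / T3

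| T3 (week) | T2 (week) | Gap (weeks) | Share |
|---|---|---|---|
| 26 | 12 | 14 | 14/26 = 54% |
| 26 | 14 | 12 | 12/26 = 46% |
| 24 | 12 | 12 | 12/24 = 50% |
| 24 | 14 | 10 | 10/24 = 42% |

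**Position relative to discharge** (T2 at week 12, T3 at week 26)

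- Discharge at week 4: 26 − 4 = 22 weeks after discharge. Covered to T2: 12 − 4 = 8 weeks (8/22 = 36%). Not covered: 14/22 = 64%.
- Discharge at week 8: 26 − 8 = 18 weeks after discharge. Covered to T2: 12 − 8 = 4 weeks (4/18 = 22%). Not covered: 14/18 = 78%.

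In both cases discharge precedes T2, so the whole gap lies after discharge.

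**What other T3 data record for this window**

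- The BDI-II asks about the past 2 weeks (Assessment). It would show worsening present at T3, but not a crisis in month 4 or 5 that had resolved by then.
- Use of other treatment would show some events that led to care. The plan treats it as a predictor (Outcomes), and the Discussion says outpatient psychotherapy after discharge is assessed and controlled. It is not planned as a harm outcome, and an event that led to no treatment need not appear there.

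So these data overlap with adverse-event collection but do not replace it.

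**The case against.** **The end of collection is inferred from an empty cell.** No text says when collection stops, and the span of 'continuously' is not defined. It could mean the whole of follow-up. This stands as a caution. The separate marks at T1 and T2 would be redundant on that reading, so a narrower one is more natural. On either reading the table needs a clarifying entry.

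**Exposure and the primary endpoint are covered.** Scheduled collection spans the 12-week program, the primary endpoint at T2, and 4 to 8 weeks after discharge on the assumed stay. The T3 claim is secondary, and safety is to be described, not tested. This also stands. Ending queries with the program is a defensible choice, and for that reason the point is an inexpensive improvement and not an error.

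**Stronger readings that the documents do not support**

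- A reader might infer that T3 yields no harm data at all. It does yield some: symptom scales, quality of life, work ability and treatment use in both arms.
- A reader might infer that the protocol names relapse as a risk of the program. Background says "Partially remitted or subclinical depression is known to be a risk for relapse" and that patients "have to wait for adequate treatment for several months". These are risks of the illness and of the gap in care, which the program is meant to bridge.
- A reader might infer that a readmission or other serious event after T2 is certain to go unrecorded, or try to count such events. The content of the forms, the definition of a serious event and the reporting route between visits are not shown, and the documents give no event rate. No count is offered here.

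**Conclusion.** The point holds as a gap in the schedule. Table 1 has no adverse-event query at T3, while the efficacy scales and a secondary hypothesis extend to T3. About 14 of 26 weeks are affected, or 42% to 54% of follow-up across the timings considered, and all of it comes after discharge if the stay is 4 to 8 weeks.

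This rests on three assumptions: that the empty T3 cell means no scheduled query, that T2 falls 12 to 14 weeks after randomization, and that 6 months is 24 to 26 weeks. Spontaneous reporting between visits may exist in the full protocol. It would narrow the gap, but it is not a systematic question put to both arms.

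The consequence is limited to safety statements that reach beyond T2. The primary analysis, sample size, power and significance level do not change.

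**What to change.** 1. In Table 1, enter adverse events at T3. Ask about adverse and serious adverse events since the patient's last completed assessment, so that patients who missed T2 are covered too. Use the trial's own definitions.
2. State what period 'continuously' covers.
3. In Statistical methods, state that serious adverse events are summarized by arm from randomization to T3.
4. If collection is not extended, limit any safety statement to the period up to T2.

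The cost is a few items in a questionnaire already given online at T3, one table entry and one or two sentences. No new visit or staff are needed. The downsides are slightly more burden on patients and recall over about 14 weeks, longer for those who missed T2. Trial status gives 1 July 2014 as the start of enrolment, so any patient already past T3 when the change is made would lack the query, and the report should give their number.
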